##### Statistical analysis

2.5.2.5

Statistical analyses will be conducted within the framework of the general linear model (GLM). For the primary clinical outcomes (e.g., subjective cognitive measures, neuropsychological test scores), a linear mixed-effects model will be used to handle the repeated-measures structure of the data throughout baseline, post-intervention, and follow-ups, with time, group, and group × time interaction as fixed effects, and subject as a random effect. This approach naturally accommodates missing data under the missing-at-random (MAR) assumption without requiring complete cases. The primary analysis will follow the intention-to-treat principle, including all randomized participants regardless of adherence or dropout, with missing values handled using multiple imputation based on baseline characteristics and available follow-up data. A per-protocol sensitivity analysis will also be conducted, restricted to participants who complete at least 80% of the intervention sessions. Covariates to be included in adjusted models will comprise age, sex, years of education, and baseline cognitive scores, selected *a priori* for their known associations with cognitive outcomes in SCD populations.

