For the neuroimaging analyses, task-related regressors will be convolved with the canonical hemodynamic response function, and motion parameters will be included as nuisance covariates. A high-pass filter of 128 s will be applied to remove low-frequency drift. At the single-subject level, voxel-wise GLM analyses will be performed to identify task-related activation patterns. Contrasts of interest (e.g., recitation versus resting baseline) will be evaluated using directional T-contrasts. At the group level, individual contrast maps will be entered into second-level random-effects models. Directional two-sample T-tests will be used for between-group comparisons, and conditions with similar activation patterns may be combined to enhance statistical power. Statistical significance will be set at *p* < 0.05, corrected for multiple comparisons using the false discovery rate (FDR) at the voxel level. For exploratory analyses, an uncorrected threshold of *p* < 0.001 may be applied. Extracted effect sizes from predefined ROIs will be further analyzed using Statistical Product and Service Solutions (SPSS). One-way analysis of variance will be used to assess condition-related differences, while Spearman’s rank-order correlation will evaluate associations between neural activation and clinical variables (e.g., years of education and Cognitive Reserve Index questionnaire (CRI-q) scores). Statistical significance will be defined as *p* < 0.05.

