### Statistical methods

2.6

The primary efficacy analysis will be conducted using generalized linear mixed-effects models to analyze repeated measures data, with adjustment for relevant covariates. Microbiome analyses will be performed using DESeq2 to identify differentially abundant taxa and linear discriminant analysis effect size to detect potential microbial biomarkers. Metabolomic data will be analyzed using partial least squares discriminant analysis, and pathway enrichment analysis will be conducted using the MetaboAnalyst platform. Multi-omics integration will be performed using Spearman correlation-based network analysis and causal mediation analysis to investigate regulatory mechanisms along the gut-brain axis. Multiple comparisons will be corrected using FDR, with a threshold of *q* < 0.05. All statistical analyses will be conducted using R (version 4.4.0; R Core Team, 2024) and SPSS (version 29.0; IBM Corp., Armonk, NY, USA), with statistical significance set at *p* < 0.05.

Given the inherent complexity and multi-layered nature of multi-omics data, if the aforementioned methods are insufficient for comprehensive analysis, we will collaborate with the institutional Artificial Intelligence Center affiliated in our hospital to implement advanced analytical approaches. These may include machine learning, network-based modeling, and partial least squares regression, among others, to construct predictive models that characterize causal or associative relationships between biological markers and clinical outcomes (e.g., cognitive function and depression). The predictive performance of different models will be systematically compared.

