Consistent with the hypothesis-generating nature of this pilot research, study outcomes are organized within a predefined inferential hierarchy. The primary outcome is designated as the principal efficacy endpoint and will serve as the main basis for evaluating intervention-related effects. The secondary outcome is pre-specified *a priori*; however, given the limited sample size typical of pilot studies, findings will be interpreted as supportive and hypothesis-generating rather than definitive. EEG, gut microbiota, and metabolomic measures are designated as exploratory outcomes. These measures are not powered for confirmatory inference and are intended primarily to generate preliminary effect-size estimates and identify candidate biomarkers for future adequately powered confirmatory trials.

Based on these findings, we anticipate that the primary outcome of this pilot trial is intervention-induced change in resting-state fMRI activation within the left medial temporal region, encompassing the hippocampus and parahippocampal gyrus, from baseline (T0) to post-intervention assessment at 6 months (T1). Increased resting-state fMRI activation in the left medial temporal region following recitation training is interpreted as reflecting enhanced cognitive reserve — the brain’s capacity to sustain normal cognitive function despite underlying neurodegenerative burden — consistent with the compensatory scaffolding framework of cognitive aging (Reuter-Lorenz and Park, 2014). We anticipate that the intervention group will demonstrate significantly greater increase in left medial temporal region activation compared to controls, with the effect expected to be more pronounced in participants with lower educational attainment — consistent with a compensatory neural response in individuals with lower a priori cognitive reserve (Stern et al., 2020).

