The anticipated secondary outcome is intervention-induced change in task-based fMRI activation within bilateral fronto-striatal regions during active recitation of Chinese classics from T0 to T1. The fronto-striatal network — encompassing the dorsolateral prefrontal cortex, anterior cingulate cortex, caudate nucleus, and putamen — supports executive control, phonological working memory, and procedural learning, all of which are recruited during complex verbal recitation tasks (Ranjan and Singh, 2025). A training-induced decrease in fronto-striatal activation during recitation is the anticipated direction of effect, interpreted as increased neural efficiency: as recitation becomes more automatized through practice, the same cognitive output is achieved with lower metabolic demand, analogous to skill-learning-related neural efficiency observed in other trained cognitive domains (Kelly and Garavan, 2005).

EEG parameters and gut microbiota/metabolomic composition are designated as exploratory outcomes. Given that the study population comprises individuals with SCD, rather than overt neurodegenerative disease, significant alterations in EEG parameters may not be observed. EEG is included as an exploratory measure to characterize the electrophysiological signature of the SCD sample at baseline, and to detect any subclinical signal changes that may warrant inclusion as a sensitive biomarker in a future confirmatory trial. For the microbiota profile, the recitation training group is expected to show increased gut microbial alpha-diversity and enrichment of beneficial genera, including *Prevotella*, *Faecalibacterium*, and *Megamonas* (Sun Y. et al., 2023), as well as increased abundance of short-chain fatty acid-producing taxa, such as *Ruminococcus*, *Roseburia*, *Subdoligranulum*, and *Bifidobacterium* (Swarup et al., 2025), compared to controls. Results will be reported descriptively, including individual-level variability data, and effect sizes with 95% confidence intervals will be provided to inform the design of a future confirmatory trial.

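### The fMRI endpoints are T0-to-T1 changes, but no section names the T0 imaging value as a covariate in the comparison of arms, and Sections 2.5.2.5 and 2.6 give different analyses

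*Protocol article*

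**What the plan says.** Section 3.3 (Anticipated outcomes) gives the primary outcome as "intervention-induced change in resting-state fMRI activation within the left medial temporal region" and the secondary outcome as "intervention-induced change in task-based fMRI activation within bilateral fronto-striatal regions", both measured from T0 to T1 at six months. It adds: "The primary outcome is designated as the principal efficacy endpoint".

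The imaging part of Section 2.5.2.5 (Statistical analysis) states that "individual contrast maps will be entered into second-level random-effects models" and that "Directional two-sample T-tests will be used for between-group comparisons". The only covariates in that part are motion parameters. Values extracted from regions of interest then go to one-way analysis of variance and Spearman correlation, again with no T0 term.

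Earlier in the same section, for the clinical scores: "Covariates to be included in adjusted models will comprise age, sex, years of education, and baseline cognitive scores". These are cognitive baselines, not imaging baselines.

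Section 2.6 (Statistical methods) states: "The primary efficacy analysis will be conducted using generalized linear mixed-effects models to analyze repeated measures data, with adjustment for relevant covariates". It does not say which covariates are relevant or whether the fMRI endpoint is covered.

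**The concern.** A T0 scan is planned for every participant, and the best use of it is as a covariate. A two-sample t-test on change scores gives the T0 value a fixed weight of 1, whatever its correlation with T1. A t-test on T1 maps alone gives it a weight of 0. A regression on T0 estimates the weight from the data and, apart from the small cost of estimating it, is never less precise than either.

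Precision is the point of this trial. The Abstract and Section 2.1 make estimation of effect sizes for later trials an aim, Section 3.3 promises effect sizes with 95% confidence intervals, and Sections 2.3 and 3.2 concede that the sample is small. Wider intervals than necessary on the endpoint called the principal one weaken the main product of the pilot.

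In addition, a reader cannot tell which of two analyses applies to that endpoint.

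**Working it through.** **The plan's own figure.** The only power calculation (Section 2.3) is for neuropsychological scores: two independent means, d = 0.18, one-sided α = 0.05, power 0.80, giving 383 per group. The exact noncentral t calculation reproduces it, with power 0.8006 at 383 per group. It says nothing about the fMRI endpoints, for which the document gives no SD, precision or correlation.

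**Inputs.** The plan is for 30 per arm, 1:1 (Section 2.3). fMRI is done at two visits, baseline and six months (Section 2.5.2.3). Two inputs are assumed: equal variances at T0 and T1 (set to 1), and a T0–T1 correlation r, shown over a range.

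**Formulas**, for the variance entering the arm comparison:
- T1 alone: 1
- change score: 2(1 − r)
- T1 adjusted for T0: 1 − r²
- precision lost by the change score relative to adjustment: 1 − (1 − r²)/[2(1 − r)] = (1 − r)/2
- precision lost by T1 alone relative to adjustment: r²
- widening of the confidence interval with the change score: √[2(1 − r)/(1 − r²)] − 1

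| r | Change score | Adjusted | Loss, change score | Interval wider by | Loss, T1 alone |
|---|---|---|---|---|---|
| 0.2 | 1.60 | 0.96 | 40% | 29% | 4% |
| 0.3 | 1.40 | 0.91 | 35% | 24% | 9% |
| 0.5 | 1.00 | 0.75 | 25% | 15% | 25% |
| 0.7 | 0.60 | 0.51 | 15% | 8.5% | 49% |
| 0.8 | 0.40 | 0.36 | 10% | 5.4% | 64% |
| 0.9 | 0.20 | 0.19 | 5% | 2.6% | 81% |

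Subtracting T0 is worse than ignoring it when 2(1 − r) > 1, that is, only when r < 0.5. Above that, subtraction helps, but less than adjustment does.

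**Finite sample.** Simulation with 30 per arm and 20,000 replicates per value of r gave losses of 33%, 24% and 13% at r = 0.3, 0.5 and 0.7. These are slightly below the formula because the slope has to be estimated.

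**In terms of this trial.** Sixty completers analysed by change score carry the information of 60(1 + r)/2 analysed with adjustment: 39, 45 and 51 at r = 0.3, 0.5 and 0.7. With 30 per arm, one-sided 0.05 and 80% power, the detectable difference is (1.645 + 0.842) × √(2/30) = 0.642 times the square root of the variance above, in SDs of a single-visit value. Adjustment lowers it from 0.76 to 0.61 at r = 0.3, from 0.64 to 0.56 at 0.5, and from 0.50 to 0.46 at 0.7.

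**Does Section 2.6 supply the adjustment?** Not as written. With two visits and complete data, a mixed model with group, time and their interaction, and T0 kept as an unconstrained outcome, gives the change-score contrast. It recovers the precision only if T0 imaging is one of the covariates or the arms' T0 means are constrained to be equal. The text states neither.

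**The case against.** The strongest objection is that Section 2.6 may already cover the primary fMRI endpoint, because Section 3.3 calls it the principal efficacy endpoint and Section 2.6 speaks of the primary efficacy analysis with covariates left open. This stands in part. A reader might infer that the plan never adjusts for T0. The documents do not support that: they leave it open and name two analyses. Against the objection, Section 2.5.2.4 puts all fMRI statistics in SPM while Section 2.6 names R and SPSS. The only listed covariates omit baseline imaging.

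Second, Section 2.5.2.5 does not say that T1-minus-T0 maps enter the t-test. That is an inference from the endpoint definitions in Section 3.3. If T1 maps alone are compared, the loss is r², which grows with r instead of shrinking. Both readings lose precision, but the figures differ.

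Third, the imaging text describes a task pipeline, whereas the primary endpoint in Section 3.3 is resting-state. Sections 2.5, 3.1 and 3.3 also describe the main fMRI measure differently. This stands: the endpoint has to be settled before its model can be.

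Fourth, second-level covariates might be left to a fuller document. That is fair for details. Here, however, the article names a specific test for imaging and a different model elsewhere.

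Three further inferences are tempting and do not hold:
- A reader might take 15–35% as the cost. It holds only for r from 0.3 to 0.7 and on the variance scale.
- A reader might infer bias. With T0 unaffected by arm, change score, T1 alone and adjusted analysis are all unbiased under randomisation.
- A reader might infer that effects will be standardised by the SD of change and so travel badly to the next trial. No section says so, and Section 2.5 gives percent signal change as the unit.

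**Conclusion.** The point holds as an efficiency recommendation and a request to reconcile two sections. The fMRI endpoints are changes, the imaging text prescribes an unadjusted two-sample test, and no section names the T0 imaging value as a covariate. If the test is on change scores, the precision lost is (1 − r)/2: from 40% at r = 0.2 to 5% at r = 0.9, and 25% at r = 0.5. If it is on T1 alone, the loss is r². These sizes assume equal T0 and T1 variances and a T0 value independent of arm, and r is unknown.

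That last assumption needs care. The Abstract places randomisation before the baseline assessment, and participants are not blinded. T0 remains a valid covariate only if it is measured before any training begins. It is a worthwhile change, but the trial is not invalid without it.

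**What to change.** State in Sections 2.5.2.5 and 2.6 which analysis governs the fMRI endpoints, and make the two agree. For each pre-specified region endpoint, name one between-group model: T1 region value = arm + T0 region value + the randomisation factors (age and sex, Section 2.1). Report the adjusted arm difference with its 95% confidence interval in percent signal units. Keep the voxel-wise two-sample maps as supportive displays, and say whether they are change maps or T1 maps. State that T0 scans are completed before any training starts.

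The cost is a few sentences, a few degrees of freedom, and maps that will not match the region model exactly. No new data are needed.

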### Outcome measurement

2.5

As described in the Sample Size section, functional MRI serves as an exploratory mechanistic outcome measure, detecting changes in task-related brain activation. The unit of measurement will be the percentage change in whole-brain blood-oxygen-level-dependent signal (%). APOE genotyping will be offered as an optional ancillary component of the study and used for exploratory analyses to investigate potential associations between genetic risk and intervention outcomes.

All other outcomes are defined as secondary outcomes, including:

changes in resting-state EEG spectral activity;performance changes across 11 neuropsychological tests;APOE genotype distribution;circulating inflammatory and stress biomarkers (IL-6, TNF-*α*, high-sensitivity C-reactive protein, and cortisol);gut microbiota diversity (Shannon index);gut microbiota taxonomic composition; andfecal metabolomic profiles related to the gut–brain axis.

Detailed methodologies for each outcome measure are described in the following sections.

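### The imaging outcomes are changes in named regions, but the only between-arm imaging test spelled out is a voxel-level FDR search; a single test on the region mean should be named instead

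*Protocol article*

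**What the plan says.** Section 3.3 (Anticipated outcomes) gives the primary outcome as "intervention-induced change in resting-state fMRI activation within the left medial temporal region, encompassing the hippocampus and parahippocampal gyrus", from baseline to six months, and treats it as the principal efficacy endpoint. The secondary outcome is "intervention-induced change in task-based fMRI activation within bilateral fronto-striatal regions during active recitation of Chinese classics from T0 to T1", in a network "encompassing the dorsolateral prefrontal cortex, anterior cingulate cortex, caudate nucleus, and putamen".

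Section 2.5.2.5 (Statistical analysis) sets out the imaging inference. Individual contrast maps enter second-level models, the arms are compared by directional two-sample t-tests, and significance is p < 0.05 "corrected for multiple comparisons using the false discovery rate (FDR) at the voxel level". It mentions no mask, small volume or other regional restriction.

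The same section extracts values from predefined ROIs. Two analyses are named for them: "One-way analysis of variance will be used to assess condition-related differences", and Spearman correlations with clinical variables such as education. Neither is said to compare the arms.

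Two mixed models appear. The one in section 2.5.2.5 is assigned to clinical outcomes. The one in section 2.6 (Statistical methods) is for the primary efficacy analysis, without saying which outcome that is.

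**The concern.** A hypothesis about one region needs one test. If the arms are compared only through a voxel-wise search, that hypothesis carries the multiplicity correction for every voxel searched. With about 30 participants per arm, this correction is expensive. A real regional effect may leave no surviving voxel, or only a few isolated ones, which is weak evidence about the region as a whole.

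The stated purpose is also affected. Section 2.1 wants effect sizes from which later definitive trials can be sized. A thresholded map does not supply that. A between-arm difference in the region mean, with a confidence interval, does. The article already plans to extract the values needed but does not say that the arms will be compared on them.

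**Working it through.** **1. The plan's own figure.** For two independent means, power = P(T > tₚ), where T is noncentral t with 2n − 2 df and noncentrality λ = d√(n/2), and tₚ is the central-t critical value. Section 2.3 gives 383 per group for d = 0.18, one-tailed α = 0.05 and power 0.80. Here λ = 0.18 × √191.5 = 2.49, and power is 0.8006, as stated. That calculation is for neuropsychological scores. The article gives no effect size for the regional imaging outcomes, so d below is an assumption, shown over a range.

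**2. Completers.** Section 2.3 enrols 72 and expects at least 60 to finish, or 30 per arm. At its 20% attrition rate, 72 × 0.8 = 57.6, or about 29 per arm. Both are used.

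**3. One test on the region mean.** At d = 0.5 and one-sided 5%:
- n = 30: λ = 0.5 × √15 = 1.94, critical t (58 df) = 1.67, power 60.6% (two-sided 47.8%).
- n = 29: λ = 0.5 × √14.5 = 1.90, power 59.3% (two-sided 46.5%).

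**4. Any one given voxel at stricter thresholds.** The FDR cut-off adapts to the data, so 0.001 and 0.0001 are illustrations. With 30 per arm, one-sided:

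| True d | α = 0.05 (one ROI test) | α = 0.001 | α = 0.0001 |
|---|---|---|---|
| 0.3 | 31% | 2% | 0.4% |
| 0.5 | 61% | 11% | 3% |
| 0.65 | 80% | 25% | 9% |
| 0.8 | 92% | 45% | 21% |
| d with 80% power | 0.65 | 1.06 | 1.25 |

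**5. The whole voxel search.** A region has many voxels, so the fairer question is whether any of them survives. Three simulations applied Benjamini-Hochberg FDR at 0.05 over the whole brain. The stated voxel size is about 3.5 × 3.5 × 4.4 = 53.9 mm³, so an assumed 1.4 L brain has about 26,000 voxels. Region size, smoothness and within-region correlation are also assumptions. Results at d = 0.5:

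| Setting | At least one region voxel survives | Share of region voxels detected |
|---|---|---|
| About 26,000 voxels, region 0.5-2% of brain, 8-12 mm smoothness, 29 per arm, 400 runs | 17-62% (22-36% for a 1% region) | 1-2% |
| About 27,300 voxels, same region and smoothness assumptions, 200 runs | 10-61% (26-39% for a 1% region) | about 1-2% |
| 29,704 voxels, region of 117 voxels (6.3 ml), 8 mm smoothing, 30 per arm, 60 runs | 5-12% | 2-3% |

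In the first setting the same d applies to the voxel and to the region mean, so the comparator is the 59% in step 3. This favours the voxel search. In the third setting, averaging voxels removes noise, and the ROI-mean test reached 70-93%. Its percentages carry a standard error of up to about 6 points. At d = 0.3 the voxel search found any region voxel in 2-9% of trials in the first two settings and 0-2% in the third, against 30-31% for one ROI test with the same d.

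**6. Effect sizes.** In the third setting, the average over the whole region recovered the truth: 0.47-0.53 for a true 0.5. Surviving voxels alone averaged 1.0-1.2.

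**The case against.** **Section 2.6 may already cover the primary.** It assigns a mixed model to the primary efficacy analysis, and section 3.3 calls its regional primary the principal efficacy endpoint. Read together, these could mean a repeated-measures comparison of the regional value. This stands as a caveat, so one cannot say that no such test exists. But section 2.6 never mentions imaging, and section 2.5.2.5 handles imaging separately. If the mixed model was intended, the article gives two analyses without linking them, and the text still needs changing.

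**The map analysis is task-based, while the primary is resting-state.** This is correct. The voxel search applies directly to the task-based secondary. For the primary, the reader is left with either the voxel search or the unlinked model.

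**Whole-brain is an inference.** Section 2.5.2.5 states no search volume, and voxel-level FDR can be run inside a mask. None is stated, however, and section 2.5 describes the fMRI measure in whole-brain terms: "The unit of measurement will be the percentage change in whole-brain blood-oxygen-level-dependent signal".

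**The size depends on assumptions.** This also stands. With the most favourable region size and smoothness, the chance of any surviving voxel (about 60%) equals the power of the ROI test, so by that lenient measure there is no loss.

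**Stakes are limited.** Section 2.5 calls fMRI exploratory, and the trial is hypothesis-generating with feasibility as a main aim. This limits the weight of the point. It does not remove it, because effect-size estimation is also a stated aim.

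**A stronger reading is tempting:** that the plan will yield inflated regional effect sizes. The documents do not support it. Effects are to be extracted from predefined ROIs, which significance does not select, and nowhere does the article say they will be read from surviving voxels. A reader might also take "effect sizes with 95% confidence intervals will be provided to inform the design of a future confirmatory trial" as a promise about imaging, but that sentence closes the paragraph on EEG and microbiota.

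**Conclusion.** The point holds as a mismatch between outcome and analysis. The imaging outcomes are regional, the one explicit between-arm imaging test is voxel-wise without a stated regional restriction, and no stated test compares the arms on the ROI values. At an assumed d = 0.5 with 29 to 30 per arm, a single ROI test has 59-61% power one-sided (47-48% two-sided). A whole-brain FDR search finds even one region voxel in roughly 5-60% of trials and detects about 1-3% of the region's voxels. The range is wide because region size, smoothness, correlation and d are not in the article.

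Two limits apply. Inflation would arise only if effects were taken from surviving voxels. In addition, the description of a single region fits only the primary: the secondary spans four structures on both sides with no summary rule, and the simulations do not represent that network. The change is worth making but is not critical to the trial.

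**What to change.** In section 2.5.2.5, with a cross-reference in section 2.6:

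- Make the between-arm comparison of baseline-to-six-month change in the mean signal of the predefined left medial temporal ROI one single test, reported as an estimate with 95% CI. If the section 2.6 mixed model is meant to provide it, say so.
- Do the same, as secondary, for one prespecified summary of the fronto-striatal regions, stating how the structures and sides are combined.
- Keep the voxel-wise FDR maps as supportive.
- State that planning effect sizes come from the whole ROI regardless of significance.
- Align the outcome wording first: section 2.5 uses whole-brain signal, section 3.1 hippocampal-default mode connectivity, and section 3.3 regional activation.

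The cost is wording only, since the ROI values are already to be extracted. The small downside is that a region mean can dilute a very focal effect. The supportive maps remain available to look for one.
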